### Sequence generation

Participants are assigned to the study group based on a diagnosis of FGR from routine fetal ultrasound and the absence of exclusion criteria. The control group comprises participants based on gestational age (≥37 + 0/7 weeks), no diagnosis of FGR on ultrasound, and the absence of exclusion criteria for this group.

### Data collection

Patients’ data are collected using a password-protected electronic form, with access restricted to the researchers involved in the study.

The researchers are responsible for conducting blood tests on the umbilical cord blood and performing both fetal and postnatal transfontanelle ultrasound examinations.

### Statistical methods

Descriptive statistics, including percentages for categorical variables and mean values, standard deviations, medians, and interquartile ranges for continuous variables, will be used to summarize the data. The Kolmogorov-Smirnov test, along with graphical analysis, will be employed to assess whether continuous variables conform to a normal distribution.

For analyzing the relationship between a quantitative variable and a qualitative variable (e.g., comparing S100B levels between the study and control groups), the Student’s t-test for independent samples will be used if the continuous variable is normally distributed. If the continuous variable does not meet the assumptions of normality, the Mann-Whitney U test will be applied instead.

To test hypotheses about the relationships between two continuous variables (e.g., S100B protein concentration versus flow rates), while accounting for confounding factors such as pregnancy duration and mode of delivery, either multivariate quantile regression or multivariate linear regression will be employed, depending on the distribution of the outcome variable.

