## Introduction

Fetal hypoxia-ischemia (HI) presents a major challenge in perinatology due to its potential for causing severe complications in the child. Hypoxemia can result in brain damage, which may lead to conditions such as cerebral palsy, epilepsy, delayed psychomotor development, intellectual disability, and cognitive impairment [1–3].

Currently, the diagnosis of neonatal HI relies on a combination of prenatal and postnatal data. Abnormal UA and MCA blood flow parameters detected prenatally may indicate a risk of fetal HI. Postnatally, the diagnosis is based on neurological examination, laboratory tests, neurophysiological assessments, and imaging studies (such as ultrasound and MRI), along with ultrasonographic evaluation of blood flow parameters in the MCA and anterior cerebral artery (ACA) [1,3]. Despite these methods, some infants with CNS damage may not show immediate symptoms or abnormalities in additional tests after birth, highlighting the need for improved early identification strategies. Cord blood biomarkers, such as the S100B, are therefore of significant interest [1–11].

S100B is a calcium-binding regulatory protein found in the cytoplasm of brain cells. In cases of CNS damage, such as hypoxia, S100B is released into the bloodstream, resulting in elevated levels in cerebrospinal fluid and umbilical cord blood [2,8,12]. This allows for the noninvasive assessment of the biomarker’s concentration immediately after birth. Due to its short half-life, S100B facilitates the recognition and monitoring of CNS damage progression, with its concentration correlating with the severity of hypoxia. Other factors that can elevate S100B levels in a newborn’s bloodstream and cord blood include chorioamnionitis, preterm birth, prolonged vaginal labor (lasting over 15 hours), and operative delivery [5,13–17]. Conversely, significantly lower S100B levels have been observed in infants born to mothers treated with selective serotonin reuptake inhibitors (SSRIs) [18].

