To account for the potential influence of the mode of delivery (vaginal delivery [VD] or cesarean section [CS]) on S100B protein concentration, the study aims to balance the proportion of neonates delivered by each method between the study and control groups. As recruitment progresses, the number of pregnancies delivered by VD and CS in the study group will be monitored. Recruitment in the control group will be adjusted based on the mode of delivery to ensure that the percentage of CS is similar in both groups. This approach aims to minimize any confounding effects of the delivery method on the study outcomes.

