### Outcome measures

The study’s primary endpoint will be the concentration of S100B protein measured from a cord blood sample taken after birth in both the study and control groups.

Additional endpoints will include:

The potential correlation between S100B concentration and pH, BE, and lactate levels, as determined in the cord blood gas analysis in both the study and control groups.The possible relationship between cord blood S100B protein concentration and blood flow parameters (PI) in the UA, UtA, DV, and MCA, as assessed by fetal ultrasound performed within 48 hours before delivery.

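### The primary FGR-versus-control comparison of S100B is unadjusted, leaving gestational age within term, a confounder the protocol itself names, neither balanced nor adjusted for

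*Protocol article*

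**What the plan says.** All references are to the protocol article.

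- **Endpoint.** Under Outcome measures, the "primary endpoint will be the concentration of S100B protein measured from a cord blood sample taken after birth in both the study and control groups".
- **Primary test.** Statistical methods gives "comparing S100B levels between the study and control groups" as its example of relating a quantitative to a qualitative variable. A Student's t-test is used if S100B is normally distributed. Otherwise: "If the continuous variable does not meet the assumptions of normality, the Mann-Whitney U test will be applied instead". No covariates are mentioned.
- **Where adjustment applies.** The next paragraph opens "To test hypotheses about the relationships between two continuous variables (e.g., S100B protein concentration versus flow rates" and plans linear or quantile regression "while accounting for confounding factors such as pregnancy duration and mode of delivery". Relations of this kind are the additional endpoints under Outcome measures.
- **Known influences on S100B.** The Introduction lists chorioamnionitis, preterm birth, "prolonged vaginal labor (lasting over 15 hours), and operative delivery" among the factors that can raise it.
- **Control of mode of delivery by design.** The text closing the eligibility criteria says: "Recruitment in the control group will be adjusted based on the mode of delivery to ensure that the percentage of CS is similar in both" (meaning the FGR and control groups). It adds: "This approach aims to minimize any confounding effects of the delivery method on the study outcomes".
- **Control of gestational age by design.** Both sets of inclusion criteria, and Sequence generation, require at least 37+0 weeks. No matching or balancing within term is stated. Study procedures and data collection says gestational age is recorded.

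**The concern.** Trial design describes a prospective cohort compared with controls, so nothing makes the two groups alike at birth except the eligibility rules and the way controls are recruited. The protocol regards pregnancy duration as a confounder in a cohort that is entirely at term, yet it uses that knowledge only in the secondary analyses.

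Suppose the FGR infants are born at a different gestational age within term from the controls, and S100B varies with gestational age over that range. The unadjusted group difference then mixes the two effects. A significant result on the first objective could be partly a gestational-age effect, and the plan as written contains no group comparison that would show it.

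**Working it through.** **Step 1. Which named factors are already controlled.**

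| Factor | Controlled by design? | In the primary test? |
|---|---|---|
| Preterm birth | Yes, at least 37+0 weeks in both groups | not needed |
| Labour over 15 hours | Yes, excluded in both groups | not needed |
| Mode of delivery | Caesarean share balanced at group level, as an aim | No |
| Gestational age within term | No | No |

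Gestational age within term is the one factor with neither kind of control.

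**Step 2. The plan's own sample size.** The target difference is 0.5 × 1.15 = 0.575. The SD is not printed, so the figure of about 55 per group cannot be reproduced independently; it can only be solved backwards. A two-sided t-test at 0.05 with 80% power and 55 per group detects d = 0.539 SD, which implies an SD of 0.575 / 0.539 = 1.067. With 60 recruited per group and 10% non-evaluable, 60 × 0.9 = 54 remain. The calculation is for an unadjusted two-group comparison, which matches Statistical methods.

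**Step 3. Size of a possible bias.** The document gives neither the gestational-age gap between groups nor the slope of S100B on gestational age within term. Both are assumptions here:

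- gap g: 0.25 to 1.5 within-group SD of gestational age;
- slope s: 0.1 to 0.2 SD of S100B per SD of gestational age.

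The spurious difference is b = g × s, in SD of S100B. With no true FGR effect, the t statistic has noncentrality b × √(54/2) = 5.196 × b on 106 degrees of freedom. The false-positive rate is the chance that it passes the two-sided 5% limit.

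| Gap g | Slope s | b | b / 0.539 | False-positive rate |
|---|---|---|---|---|
| 0.25 | 0.1 | 0.025 | 5% | 5.2% |
| 0.25 | 0.2 | 0.05 | 9% | 5.8% |
| 0.5 | 0.1 | 0.05 | 9% | 5.8% |
| 0.5 | 0.2 | 0.10 | 19% | 8.1% |
| 1.0 | 0.1 | 0.10 | 19% | 8.1% |
| 1.0 | 0.2 | 0.20 | 37% | 18% |
| 1.5 | 0.1 | 0.15 | 28% | 12% |
| 1.5 | 0.2 | 0.30 | 56% | 34% |

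A regression that includes gestational age, if its form is right, holds the rate at about 5%.

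**Step 4. Price of adjustment.** With equal groups, the variance of the adjusted group difference is inflated by 1 + g²/4. The small gain from explained variance is ignored. Power is for d = 0.539 at 54 per group.

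| Gap g | Inflation | Effective n per group | Power |
|---|---|---|---|
| 0 | 1.00 | 54 | 79% |
| 0.5 | 1.06 | 51 | 77% |
| 1.0 | 1.25 | 43 | 70% |
| 1.5 | 1.56 | 35 | 60% |

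**The case against.** **Much is handled by design.** Preterm birth and long labour are excluded in both groups, and control recruitment is steered to equalise the caesarean share. A reader might infer that two named confounders are left uncontrolled. For mode of delivery the documents do not support this. Leaving a balanced factor out of a two-sample test costs precision and does not bias the difference. What remains is that the balancing is an aim at group level and is described only for the caesarean share.

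**No gradient within term is documented.** The Introduction speaks of preterm birth only. It does not say that S100B falls between 37 weeks and later term, and no passage says that FGR infants will be born earlier than controls. This stands as a limit on the size of the problem. It does not remove the problem, because Statistical methods itself lists pregnancy duration as a confounder in this all-term cohort.

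**The unadjusted comparison may be the intended one.** The first objective asks whether S100B is higher in FGR neonates than in controls, and the closing limitations speak of associations. Gestational age at delivery and mode of delivery can be consequences of FGR, so adjusting for them may remove part of what FGR does. This stands. It is the reason to report both estimates rather than discard the unadjusted one.

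**An analysis plan may add adjusted group comparisons.** It may. But the article names the test for the primary comparison and says where adjustment applies, so this is a stated choice and not merely detail left for later.

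**Conclusion.** The point holds for gestational age. Followed as written, the plan tests its primary hypothesis in a non-randomised comparison without controlling a confounder that it names and records.

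The effect may be negligible or serious. Under the assumed ranges the false-positive rate runs from about 5% to 34%. At gaps of 0.25 to 0.5 SD it stays at about 5% to 8%. A reader might take the upper figures as the expected error rate, but rates above 20% arise only with the assumed gap of 1.5 SD, and nothing in the document says that the groups will differ by so much.

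Nor do the documents support reading the t-test or Mann-Whitney test as invalid: it answers whether S100B differs between the groups as they are born. What it cannot support alone is a claim that S100B is higher because of FGR.

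**What to change.** Before any group results are seen, add to Statistical methods a linear or quantile regression of S100B on group, with gestational age at delivery and mode of delivery as covariates. Report the adjusted group difference with its 95% CI beside the t-test or Mann-Whitney result. State that any claim of higher S100B because of FGR rests on the adjusted estimate, and that this estimate may exclude a part of the association that acts through earlier delivery.

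The cost is mainly wording. Both regression methods are already planned and both covariates are already collected. The statistical cost is the loss of power shown in the working, which is small unless the groups differ markedly in gestational age. Study setting puts enrolment at about two-thirds in both groups as of September 2025. Where control recruitment is still open, balancing controls on gestational week as well as mode of delivery would limit the loss. If it has closed, the loss has to be accepted and shown in the width of the interval.

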#### Control Group – Exclusion criteria.

Antenatal (at recruitment):Maternal conditions that may affect placental blood flow, such as smoking, use of illicit stimulant substances, pregestational diabetes, or chronic hypertension.Maternal depression requiring pharmacological treatment (e.g., SSRIs).Risk factors for intrauterine HI, including abnormal fetal blood flow parameters on ultrasound, abnormal CTG recordings, or the need for intrauterine transfusion (IUT).Intrapartum:Indicators of possible intrauterine infection, such as amniotic fluid leakage for more than 15 hours, spontaneous preterm delivery, diagnosed intrauterine infection, or maternal symptoms of infection.Risk factors for perinatal HI.Prolonged labor lasting more than 15 hours (counted from the onset of regular uterine contractions).Birth weight below the 10th percentile or above the 90th percentile.Apgar score less than 8 at the 1st, 3rd, 5th, or 10th minute of life.Abnormal umbilical cord blood gas analysis results, defined as pH < 7.15 or BE < −9.3 mmol/l.Postnatal:Neonatal anemia requiring a top-up transfusion within the first 24 hours of life.

The exclusion criteria for the study and control groups differ based on the principle that the control group should consist of healthy neonates without risk factors for HI. In contrast, the study group includes infants diagnosed with FGR, who inherently have a higher risk of complications. These complications, such as a low Apgar score, abnormal umbilical cord blood gas analysis parameters, or an abnormal CTG recording, are precisely the factors that serve as exclusion criteria for the control group. This approach ensures that the control group provides a valid baseline for comparison against the at-risk study group.

In patients with a singleton, full-term pregnancy who present to the labor and delivery unit and meet the inclusion criteria, without meeting the antenatal exclusion criteria (except for those related to FGR), informed written consent for testing is obtained prior to delivery. The mother is also informed that if any exclusion criteria are identified during or after delivery, the child will be disqualified from further participation in the study.

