### Sample size

The estimated minimum total sample size for the study is 120 patients, with 60 participants in each group. The planned sample size was determined for a two-sided comparison between two independent groups, assuming a significance level of 0.05, statistical power of 80%, and equal group sizes. The variability of the primary biomarker (S100B) was estimated based on data from a previously published reference study [12], which reported median values together with the 10th and 90th percentiles. As standard deviations were not provided, dispersion was approximated from the reported percentiles under an approximate normality assumption, following established methods for recovering variability from limited summary statistics [26,27]. In the reference study, the observed difference between group medians was 1.15. However, since group allocation in that study was performed retrospectively on the basis of cranial imaging findings (brain injury vs. no brain injury), a conservative approach was adopted in the present sample size estimation to minimize the risk of effect size overestimation. Therefore, the target detectable difference was defined as 50% of the previously reported median difference.

Based on these assumptions, the estimated required sample size was approximately 55 participants per group. Additionally, considering that up to 10% of collected samples could be non-diagnostic or otherwise non-evaluable, the planned recruitment target was increased to 60 participants per group (120 participants in total). Sample size calculations were performed using standard power analysis procedures implemented in G*Power software (version 3.1.9.4).

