## Study strengths, limitations and future directions

To address the knowledge gap, the study aims to answer the following questions:Is cord blood S100B protein concentration significantly higher in infants with prenatally diagnosed late FGR, a condition associated with increased risk of hypoxic CNS injury?Does the concentration of S100B protein in umbilical cord blood correlate with blood flow parameters in the UA, UtA, DV, and MCA, as assessed by ultrasound within 48 hours before delivery?Is there an association between S100B protein concentration and pH, BE, and lactate levels in cord blood, in the context of evaluating perinatal hypoxic stress?The study procedures are straightforward and confined to a specific time point, which facilitates the accurate implementation of the study protocol.The study evaluates only short-term outcomes and does not account for the long-term neurological development of the children.In cases of urgent indications for delivery or an advanced stage of labor at admission, performing a reliable Doppler flow assessment may not be feasible.In some instances, collecting the necessary volume of cord blood for testing may be difficult due to technical problems.Due to numerous exclusion criteria in both the control and study groups, which may arise after informed consent is obtained, some patients may be disqualified during the study.

The present study may serve as a starting point for further investigations into the usefulness of S100B protein as a biomarker associated with the risk of hypoxia-related CNS injury in neonates with late FGR. Future research should consider extending the diagnostic approach to include long-term neurological follow-up, as well as additional assessment of cerebral blood flow using postnatal ultrasonography and monitoring of cerebral bioelectrical activity with amplitude-integrated electroencephalography (aEEG). Such an approach could enable evaluation of the relationship between perinatal S100B protein concentrations and subsequent neurodevelopmental outcomes in children with FGR.

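### The parametric test for the primary S100B comparison should be Welch's, not Student's: the FGR spread may be wider than the control spread, and evaluable numbers may end unequal

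*Protocol article*

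**What the plan says.** Statistical methods (protocol article) gives the comparison of S100B between the study and control groups as its example of a quantitative variable set against a qualitative one. S100B concentration is the primary endpoint under Outcome measures. The Student's "t-test for independent samples will be used if the continuous variable is normally distributed"; if normality fails, the Mann-Whitney U test replaces it. Normality is judged by a Kolmogorov-Smirnov test and graphs. The section mentions no check of equal variances, no unequal-variance version of the test and no confidence interval for the group difference.

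The control exclusion criteria rest on the principle that "the control group should consist of healthy neonates without risk factors for HI". Controls are removed for abnormal fetal flow or CTG, an Apgar score below 8, cord pH < 7.15 or BE < −9.3 mmol/l, and birth weight outside the 10th to 90th percentile. The same section explains that low Apgar scores, abnormal cord gases and abnormal CTG are expected complications in the FGR group, where they do not exclude.

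Sample size plans a "two-sided comparison between two independent groups", "assuming a significance level of 0.05, statistical power of 80%, and equal group sizes". Losses after consent are anticipated: "Due to numerous exclusion criteria in both the control and study groups, which may arise after informed consent is obtained", some patients may be disqualified.

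**The concern.** Student's t-test uses one pooled variance. It needs either equal variances or, failing that, equal group sizes. Here both could fail.

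- **Spread.** The Introduction says that S100B correlates with the severity of hypoxia and that, within FGR, it is higher when umbilical artery flow is abnormal than when it is normal. The FGR definition admits fetuses with and without abnormal flow, while controls with signs of hypoxia are taken out. On the protocol's own reasoning the FGR group may therefore be the more variable one.
- **Numbers.** Study setting reports fewer FGR pregnancies and more exclusions than expected, and some exclusions are applied only during or after delivery. Equal evaluable numbers are planned but not assured.

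If the more variable group is the smaller one, the pooled standard error is too small and the test rejects too often. If it is the larger one, the standard error is too large and power is lost. The planned normality check detects neither situation.

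**Working it through.** **1. The plan's own figure.** Sample size gives a two-sided 5% level, 80% power and 1:1 groups. It states that "the observed difference between group medians was 1.15" and that "the target detectable difference was defined as 50% of the previously reported median difference", so the target is 0.5 × 1.15 = 0.575. On spread it says only "As standard deviations were not provided, dispersion was approximated from the reported percentiles under an approximate normality assumption"; no SD is printed. The figure of about 55 per group therefore cannot be reproduced forwards. Solved backwards with n = 2(1.96 + 0.842)² SD²/0.575², n = 55 implies a common SD of 1.076 (1.067 with the exact t-test). This is one implied SD and says nothing about a difference in spread between the groups.

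**2. Why equal groups protect the test.** Let s₁ be the FGR SD, s₂ the control SD, and n₁ and n₂ the evaluable numbers.

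- Expected pooled squared SE: [((n₁−1)s₁² + (n₂−1)s₂²)/(n₁+n₂−2)] × (1/n₁ + 1/n₂)
- True squared SE: s₁²/n₁ + s₂²/n₂

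With n₁ = n₂ = n, both equal (s₁² + s₂²)/n, whatever the SD ratio.

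**3. Unequal groups, worked at an assumed SD ratio of 2 (s₁ = 2, s₂ = 1).**

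- FGR 45, controls 60: pooled = [(44×4 + 59×1)/103] × (1/45 + 1/60) = 2.282 × 0.03889 = 0.0887. True = 4/45 + 1/60 = 0.1056. SE ratio = √(0.0887/0.1056) = 0.917, so the test is too liberal.
- FGR 60, controls 45: pooled = [(59×4 + 44×1)/103] × 0.03889 = 2.718 × 0.03889 = 0.1057. True = 4/60 + 1/45 = 0.0889. SE ratio = 1.091, so the test is too conservative.

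**4. True two-sided level of the nominal 5% test.** Normal data, no true difference, 60,000 simulated trials per cell (simulation error about 0.1 percentage points). SD ratios and group sizes are assumptions.

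| FGR v control | SD ratio | Pooled SE / true SE | Student | Welch |
|---|---|---|---|---|
| 55 v 55 | 1.5 | 1.000 | 5.0% | 5.0% |
| 55 v 55 | 2 | 1.000 | 5.1% | 5.0% |
| 54 v 60 | 1.5 | 0.980 | 5.5% | 5.0% |
| 54 v 60 | 2 | 0.969 | 5.8% | 5.0% |
| 45 v 60 | 1.5 | 0.946 | 6.6% | 5.1% |
| 45 v 60 | 2 | 0.917 | 7.5% | 5.2% |
| 60 v 54 | 1.5 | 1.021 | 4.7% | 5.1% |
| 60 v 54 | 2 | 1.032 | 4.5% | 5.2% |
| 60 v 45 | 1.5 | 1.057 | 3.9% | 5.1% |
| 60 v 45 | 2 | 1.091 | 3.3% | 4.9% |

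A separate simulation gave 5.4-5.9% at 54 v 60, 6.4-7.4% at 45 v 60 and 3.3-4.1% at 60 v 45. The two sets agree to within about 0.2 points. Averaging the rejection probability numerically over the distribution of the two sample variances gives 6.4% and 7.3% at 45 v 60, so the lower set is the better guide there.

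**5. Power.** At 55 v 55, difference 0.575 and common SD 1.067, both tests have 79.9% power. At 55 v 55 with SDs 1.35 (FGR) and 0.68 (control), Student has 80.3% and Welch 80.1%. At 50 FGR v 60 controls with those SDs, Student shows 80.4% and Welch 77.0%, but Student's apparent gain comes from an inflated level: 6.4% at that size and an SD ratio of 2.

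**The case against.** The strongest reply is that nothing in the article shows a problem. No group SDs are given. The control filters act on Apgar score, cord gases, CTG, flow and birth weight, not on S100B, and the Introduction calls the evidence on S100B in growth-restricted newborns sometimes contradictory. The plan is 60 per group, and Study setting reports about two-thirds of target enrolled in both groups by September 2025. At 54 v 60 the drift is under one percentage point. The choice between pooled and unequal-variance tests is also a detail that an analysis plan, not shown here, often settles. Finally, a mixture of unaffected and hypoxic FGR neonates would tend to be skewed, which may send the data to the Mann-Whitney test.

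Most of this stands, and it limits the point. A reader might infer any of the following, and the article does not support them:

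- **That the design guarantees unequal spreads.** This is a plausible inference, not a documented fact.
- **That the FGR group is unrestricted.** It has its own exclusions, among them smoking, pregestational diabetes, treated depression, signs of infection and labor over 15 hours. Only the hypoxia-related ones are missing.
- **That any inequality in numbers invalidates the test.** A material error needs both a clear difference in spread and an imbalance of roughly 45 v 60.
- **That false positives are the likely result.** The longer control exclusion list points to fewer controls, which makes the test conservative. The low FGR incidence points the other way.
- **That a planned confidence interval is wrong.** None is specified for the group difference.
- **That the regressions share the fault.** They are described as relating two continuous variables with adjustment for factors such as pregnancy duration and mode of delivery; no group term is stated.

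What does not stand is leaving the whole matter to an unseen analysis plan. The article itself names the test and the condition for using it, and a better choice is available at no real cost.

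**Conclusion.** The point holds as a minor, free improvement. The article fixes the pooled-variance test for the primary comparison with normality as its only condition, in a design where a larger FGR variance is plausible. If the evaluable numbers stay equal, the choice does not matter. If they do not, and the FGR/control SD ratio is 1.5 to 2, the nominal 5% level becomes about 5.4-5.9% at 54 v 60, 6.4-7.4% at 45 v 60, or 3.3-4.1% at 60 v 45. These figures rest on assumed SD ratios, assumed final numbers and normally distributed data. The article fixes none of these, and the direction of any imbalance cannot be foreseen. The point has no bearing on the Mann-Whitney branch.

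**What to change.** In Statistical methods, replace the Student's test for independent samples by Welch's t-test (unequal variances) in the normal branch, and state that the mean difference will be reported with its Welch 95% CI. No preliminary variance test is needed, because Welch's test holds its level whether or not the SDs are equal.

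The cost is one phrase and one added sentence. Sample size and data collection are untouched, and power at 55 per group with equal SDs is the same (79.9% for both tests). The change should be recorded before the S100B data are analysed.
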